### 7.6 Treatment Interruptions

At the discretion of the treating clinician, patients can recommence study drug following omitted dose(s) up until Week 10 and after consent to continue treatment after week 10. The treatment interruption guidelines will also apply should treatment fall over a public holiday (e.g. Easter break) and due to logistics a patient is unable to attend a hospital visit and receive study drug.

### 7.7 Treatment Compliance

ILB will be administered subcutaneously to patients at the site; they will receive study treatment directly from the investigator or designee (as documented on the study delegation log), under medical supervision. The date and time of each dose administered in the clinic will be recorded in the source documents.

The full and accurate record of drug preparation, (batch numbers, and time of preparation, dispensing and time of actual administration) will be maintained by the individual site pharmacy. This information will be provided to the sponsor upon request and some information will be recorded in the case report

forms. Full drug accountability records will be maintained by the participating site and some of this information will also be recorded within the case report forms.

Please refer to the current ALS pharmacy manual.

## 7.8 Treatment Discontinuation

See Patient Stopping Rules and Trial Stopping Rules (see protocol page (xiv))

## 7.9 Treatment after the end of the study

See protocol page (xiv) Rescue Medication

## 7.10 Supportive Treatment

See RESCUE MEDICATION page (xiv) of the protocol

## 7.11 Concomitant Medication

Patients may continue with previous concomitant treatments (i.e. prescription, non-prescription or alternative therapies) at the same doses and schedule as prior to the start of trial treatment, at the discretion of the local investigator provided the medication is not prohibited within the exclusion criteria for trial participation.

All medication that each participant is taking at the time, and within 3 months prior, to enrolment will be recorded. New medications or changes to current medications during the trial will also be recorded.

The pharmaceutical/trade name, dose, route of administration, indication, start/stop date of each new medication within the trial will be recorded. Any drug that is licensed within the United Kingdom and Europe, that is deemed necessary for the participant's health-care, will be permitted at the discretion of the Chief Investigator.

## 7.12 Prohibited Medication

The following medications or therapies are prohibited:

- Any other investigational medicinal or biological product, within 3 months of screening
- Use of Riluzole within 28 days of 1st dose of ILB
- Use of Riluzole during study treatment. Patients considered suitable to commence Riluzole following discontinuation of study treatment must have a  $\geq 7$  day wash-out period between the last dose of ILB and the first dose of Riluzole
- Any use of antioxidants, edaravone, tirasemtiv or CK-2127107 within 1 month before the screening visit
- Any botulinum toxin use within 3 months before the screening visit
- Current use of an anticoagulant e.g Warfarin, Aspirin, Clopidogrel, any novel anticoagulants (NOAC)s or low molecular weight subcutaneous heparin

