### 1.1.4 Mechanism of action

Motor neurone dysfunction and degeneration in ALS involves several pathogenic mechanisms, which include disturbed energy metabolism, cytoskeletal abnormalities, changes in transcription, glutamate excitotoxicity, glial hyper activation and reduced glutamate uptake. In our in vitro models we found that ILB is able to modulate molecular processes relevant to ALS generally enhancing the protective effect of growth factors. In glial cells the ILB reduces oxidative stress, mitochondrial dysfunction and glial activation. It also promotes cell survival, differentiation, myelin basic protein (MBP) expression and glutamate uptake. In neuronal cultures ILB reduces neuronal cell death, oxidative stress and mitochondrial dysfunction. In neurones the compound also promotes differentiation, neurite outgrowth and cellular homeostasis. Most importantly glutamate production and release in neuronal cells is NOT affected by ILB.

Glutamate production and release (followed by Ca-mediated signalling cascades) in neuronal cells is one of the most important factors required for synaptic remodelling necessary for regeneration and repair of neuronal networks affected in ALS (and indeed all neurodegenerative diseases). This process is controlled by the growth factors modulated by ILB and leads to the neurite outgrowth and differentiation of these cells. This is the process that will lead to a measurable functional benefit in the nervous system and clinical improvement in the patients.

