## 2.5 Exploratory Outcome Measures

- HPLC analyses of purine-pyrimidine metabolites (serum)
- HPLC analysis of fat-soluble vitamins and antioxidants (serum)
- HPLC analyses of amino acids (AA) and amino-group containing compounds (ACCG) (serum)
- Spectrophotometric analysis of lactate
- PBMC samples will be collected for analysis of change in phenotypic balance
- HGF release in plasma following ILB administration (ELISA from PK samples)
- Creatine kinase and Myoglobin from plasma as markers of muscle atrophy associated with ALS

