#### 7.1.6 Patient Stopping Rules

Patients will have treatment of ILB stopped if any of the following prospective criteria are met during the treatment period:

- The patient experiences a Serious Adverse Event related to IMP
- If there is a decrease in ALSFRS-R score (>50%) compared to baseline
- If a patient becomes pregnant during the study treatment period
- Unacceptable toxicity – any adverse event which, in the investigators opinion, requires termination of the study drug
- Unforeseen events – any event which in the judgement of the Investigator makes further treatment inadvisable
- SAE requiring discontinuation of treatment
- If a patient requires an anticoagulant e.g Warfarin, Aspirin, Clopidogrel, any novel anticoagulants (NOAC)s or low molecular weight subcutaneous heparin during the clinical trial
- PTT or aPTT > 1.5 x ULN
- INR > 1.8 x ULN

Patients, who stop weekly dosing, will be invited to remain in the observational part of the study up to 24 weeks, to enable assessment of safety related measures. Patients that discontinue ILB and subsequently start or re-commence Riluzole therapy will also be invited to remain in the observational part of the study up to 24 weeks.

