## 7.4 Sample Collection

### 7.4.1 Blood samples

#### 7.4.1.1 Pharmacokinetic samples

For all patients, blood samples for the determination of ILB levels will be collected as detailed in the Schedule of Assessments in the study protocol.

Samples (plasma) for PKs should be collected from whole blood, collected in anti-coagulant-treated Vacutainer tubes (3.2% sodium citrate (blue-topped)). Serum should not be prepared.

Samples for ILB measurements should be sent (single/few batches) to:

Eurofins BioPharma Product Testing Munich GmbH  
[name]  
[name]  
[name]  
Germany  
[contact] (phone)  
[[contact]](mailto:[contact])

| Time Point                                   | Blood Sample Type | Volume of blood (ml) |
|----------------------------------------------|-------------------|----------------------|
| Pre-dose (30 minutes prior to ILB injection) | Blood Plasma      | 14                   |
| 30 minutes post-injection                    | Blood Plasma      | 3.5                  |
| 60 minutes post-injection                    | Blood Plasma      | 3.5                  |
| 120 minutes post –injection                  | Blood Plasma      | 3.5                  |
| 150 minutes post-injection                   | Blood Plasma      | 3.5                  |
| 180 minutes post-injection                   | Blood Plasma      | 3.5                  |
| 240 minutes post-injection                   | Blood Plasma      | 3.5                  |
| 360 minutes post-injection                   | Blood Plasma      | 3.5                  |

Please use the current version of the laboratory manual for further information.

The remaining PK samples should be stored in a -80°C freezer and will be shipped in batches for HGF measurement (exploratory biomarker) to the Neuregenix laboratory.

**7.4.1.2 NfL levels** (performed prior to administration of study drug)

- 10mls Whole Blood collected in EDTA-treated Vacutainer tubes (lavender/purple top) (to allow for 4-5mls plasma for analysis).

Samples should be stored in a -80°C freezer and will be shipped in batches to Sahlgrenska University Hospital, (Neurokemi lab), Gothenburg, Sweden

Please see the latest version of the laboratory manual for further information

**7.4.1.3 Exploratory Biomarker Blood Samples** (performed prior to administration of study drug)

Exploratory biomarker samples for:

- HPLC analysis of purines, pyrimidines, oxidative/nitrosative stress compounds (n = 60)

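### The antioxidant ban in section 7.12 ends at the screening visit, and no other section states one during ILB treatment, although serum antioxidants and oxidative-stress compounds are exploratory markers

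*Protocol*

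**What the plan says.** Section 7.12 of the protocol gives the list of prohibited medications. Its antioxidant entry reads "Any use of antioxidants, edaravone, tirasemtiv or CK-2127107 within 1 month before the screening visit". Exclusion criterion 6, in section 4.1 and in the synopsis, has the same wording and the same window.

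Other agents are handled differently. Section 7.12 separately bars "Use of Riluzole during study treatment". For anticoagulants, section 7.1.6 makes a need for one a reason to stop ILB ("If a patient requires an anticoagulant e.g Warfarin" and other examples), and section 4.2 excludes users from the treatment extension.

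Section 7.11 governs other concomitant medication. Earlier treatments may continue at unchanged dose and schedule, at the investigator's discretion, "provided the medication is not prohibited within the exclusion criteria for trial participation". For new treatments it says "New medications or changes to current medications during the trial will also be recorded". It also allows licensed drugs considered necessary for the patient's care, at the Chief Investigator's discretion.

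The exploratory outcomes in section 2.5 include serum fat-soluble vitamins and antioxidants by HPLC. Section 7.4.1.3 and Appendix 11 add oxidative and nitrosative stress compounds.

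**The concern.** The trial assays the class of substance that it excludes at entry, and the exclusion as written does not extend to the period when most of the assays are done.

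Section 1.1.4 gives the expected direction of effect in cell models: "In glial cells the ILB reduces oxidative stress, mitochondrial dysfunction and glial activation". Appendix 11 presents the marker panel as a source of insight into how ILB works in these patients. A vitamin or antioxidant supplement started during dosing can change the measured vitamin and antioxidant levels directly. It could also move oxidative-stress compounds in the direction expected of ILB.

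Section 3 describes a single-arm, uncontrolled study, so no concurrent group would reveal such a shift. The healthy reference values considered in Appendix 11, which may be archived and unmatched, would not reveal it either. What is at stake is how these exploratory markers are interpreted.

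**Working it through.** The protocol states no figure on this point, so the check is a comparison of text.

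**1. Is there an on-treatment rule anywhere?**

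| Place | Riluzole | Anticoagulants | Antioxidants, edaravone |
|---|---|---|---|
| 4.1 entry criteria | Stopped at least 28 days before entry | Current use excluded | Month before screening only |
| 4.2 extension criteria | Not named | Use excluded | Not named |
| 7.1.6 stopping rules | Not a reason to stop ILB | Need for one stops ILB | Not named |
| 7.12 prohibited list | Before and during treatment, with a washout after ILB | Current use | Month before screening only |

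No row states an on-treatment rule for antioxidants or edaravone.

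**2. Does section 7.11 supply one?** Its proviso applies to treatments that the patient was already taking, and it refers to the exclusion criteria. For antioxidants that leads back to criterion 6 and the same pre-screening month. New medications are to be recorded, with no statement on whether they are allowed. The licensed-drug permission does not settle the status of a supplement that a patient starts without advice. Such use is neither clearly permitted nor clearly barred.

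**3. Are the markers sampled on ILB?** Yes. Section 7.2 places an exploratory blood sample at Week 5, a dosing visit, and both the Schedule of Assessments and the table in section 7.4.1.3 list it. Extension patients are sampled again on treatment at Week 24.

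**4. Can the number of affected samples be given?** No, for two reasons.

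- The sources disagree on the draw at the end of the 10-week course. The Schedule has Week 10, which is on ILB, as well as Week 12. The table in section 7.4.1.3 has Week 11 for extension patients and Week 12, off ILB, for those stopping. For a patient stopping at Week 10, that is two post-baseline draws on ILB (Weeks 5 and 10) or one (Week 5). For 15 planned patients it is 15 × 2 = 30 or 15 × 1 = 15.
- Both totals count scheduled draws. Only draws taken after a patient has started a supplement matter, and the protocol does not say how often that happens. The number could be zero.

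**5. Can exposure be identified afterwards?** Largely. Section 7.11 requires start and stop dates for each new medication, and the Concomitant Medication Form in Table 3 collects them. This depends on sites having recorded supplements as medications.

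**The case against.** The strongest reply is that section 7.12 sits in the treatment chapter and declares its items prohibited, so the named agents are banned throughout and the time windows merely carry over the entry washouts. The same literal reading would also leave botulinum toxin and other investigational products open during dosing, which was surely not intended. Riluzole may have its own on-treatment wording only because patients could be taking it up to consent and could start it after ILB.

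This shows that a continuing ban may have been intended. It does not show that one was written, because on that reading the explicit time limit in the bullet has no effect. In the other direction, a reader might infer that the protocol permits antioxidants on ILB. The text does not support that either; the rule is unclear.

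Three further replies stand in whole or part:

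- The confounder is recorded, so it can be handled in the analysis. This is correct, and the main remedy relies on it.
- A sensitivity summary is normally left to the analysis plan, which is not at hand. Its absence from the protocol is therefore not the point made here. The point is the window fixed in section 7.12; the summary is offered as the remedy still available.
- The consequence is small. No stopping rule uses these markers, the protocol documents no supplement use or assay shift, and it does not say that exclusion 6 was meant to protect the assays.

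**Conclusion.** The point holds as a low-cost improvement. The stated ban on antioxidants and edaravone ends at screening, and no section states an on-treatment ban, in contrast with riluzole and anticoagulants.

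The possible bias is confined to the exploratory serum vitamin/antioxidant results and, less certainly, the oxidative/nitrosative stress results. Its size is unknown. It rests on two assumptions that the protocol does not quantify: that some patients started a supplement during treatment, and that the supplement moved the assays.

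A reader might be tempted to treat 30 draws as uncovered. That figure should not be used, for the reasons in step 4 of the check. A reader might also infer a threat to safety, tolerability, ALSFRS-R, ALSAQ-40, urinary p75ECD or plasma NfL. Nothing in the protocol supports that, and no assay effect is claimed for tirasemtiv or CK-2127107. Edaravone is included only because the bullet groups it with antioxidants.

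**What to change.** **For data already collected.** Dosing ended in March 2020 (section 11), so new wording cannot change these samples. Use the recorded concomitant-medication start and stop dates to flag every serum sample taken during antioxidant, vitamin or edaravone use. Report the vitamin/antioxidant and oxidative/nitrosative stress results with and without the flagged samples. Naming vitamins matters because the word antioxidants may not cover all of those assayed. The flag should also cover the Week 1 pre-dose sample, since up to 14 days (28 for prior riluzole users) can pass between screening and Day 1, and the off-drug samples in follow-up.

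**For any further dosing or a follow-on protocol.** Add *and during study treatment* to the end of the section 7.12 bullet, in line with the riluzole entry, and keep the section 7.11 exception for licensed drugs judged necessary. Patients who have stopped ILB and are only under observation need not be restricted.

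**Cost.** One clause, one variable derived from dates already held, fewer samples in the sensitivity summary, and a small extra restriction on future patients while they are dosed.

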## 7.13 Contraception and Pregnancy

All WOCBP must agree to use a highly effective method of contraception as defined in the HMA\_CRFG guidelines (see Appendix 8) from the Screening visit and throughout the trial period and following the

last dose of study drug. Lactating women must agree to discontinue breast feeding before trial investigational medicinal product administration.

For the purposes of this trial, a female patient of childbearing potential is a woman who has not had a hysterectomy, bilateral oophorectomy, or medically-documented ovarian failure. Women  $\leq 50$  years of age with amenorrhea of any duration will be considered to be of childbearing potential.

Men, if not vasectomised, must agree to use barrier contraception (condom plus spermicide) during heterosexual intercourse from screening through to trial completion and from the last dose of trial investigational medicinal product.

Refer to section 8.1.2.1 if a pregnancy is reported, either that of a female participant, or the partner of a male participant.

#### 7.14 Patient Follow Up

This follow up schedule is based on patients who discontinue treatment after 10 weeks of drug administration..

##### End of treatment visit (Week 12) (Day 78 $\pm$ 3 days)

##### Visit 12

##### (2 weeks after last dose of IMP)

- ALSFRS-R
- Concomitant drug history
- Vital signs (blood pressure, heart rate, body temperature, pulse oximetry and respiration rate). Results of oximetry should be the average of three recordings. Body weight and Body Mass Index (BMI)
- ECG
- Lung Function Tests (FVC)
- SNIP
- Haematology tests (FBC, ESR)
- Coagulation tests (to include INR, APTT and PT)
- Biochemistry tests (Troponin I, C-reactive protein (CRP), Glucose, Calcium)
- Creatinine Kinase
- Urea & Electrolytes (U&Es), Liver Function Tests (LFTs)
- Thyroid Function Tests (TSH, Free T4)
- Immunoglobulins (IgG, IgM)
- Quality of Life questionnaire (ALSAQ-40)
- Urinary p75ECD
- NfL levels
- Collection of exploratory biomarker blood samples
- Pregnancy test for WOCBP
- Adverse Event assessment/reporting

An end of treatment visit must be performed 2 weeks from the last dose of ILB regardless of how many treatment doses a patient has received.

In the event a patient discontinues treatment prior to the end of week 10 the follow up schedule as detailed in the Schedule of Assessments 1 should be followed using the Week 16 schedule as a guide for visits. If drug administration ends at week 10, follow up visits should continue every 4 weeks from week 12 at which point patients should continue with the follow up schedule as per the Schedule of Assessments 1 table. i.e. week 12, week 16, week 20 and week 24 follow up visits.

If drug administration is approved to continue after week 10 but the patient discontinues early, prior to the end of week 24, follow up visits should continue every 4 weeks until week 24 where an end of treatment visit will occur.

Follow up schedule for patients who finish treatment at week 10

#### Week 16

##### Visit 13

- ALSFRS-R
- Concomitant drug history
- Vital signs (blood pressure, heart rate, body temperature, pulse oximetry and respiration rate). Results of oximetry should be the average of three recordings. Body weight
- Haematology tests (FBC, ESR)
- Coagulation tests (to include INR, APTT and PT)
- Biochemistry tests (Troponin I, C-reactive protein (CRP), Glucose, Calcium)
- Urea & Electrolytes (U&Es), Liver Function Tests (LFTs)
- Quality of Life Questionnaire (ALSAQ-40)
- Adverse Event assessment/reporting

**Week 20****Visit 14**

- ALSFRS-R
- Concomitant drug history
- Vital signs (blood pressure, heart rate, body temperature, pulse oximetry and respiration rate). Results of oximetry should be the average of three recordings. Body weight
- Haematology tests (FBC, ESR)
- Coagulation tests (to include INR, APTT and PT)
- Biochemistry tests (Troponin I, C-reactive protein (CRP), Glucose, Calcium)
- Urea & Electrolytes (U&Es), Liver Function Tests (LFTs)
- Quality of Life Questionnaire (ALSAQ-40)
- Adverse Event assessment/reporting

**Week 24****Visit 15**

- ALSFRS-R
- Concomitant drug history
- Vital signs (blood pressure, heart rate, body temperature, pulse oximetry and respiration rate). Results of oximetry should be the average of three recordings. Body weight and Body Mass Index (BMI)
- ECG
- Lung Function Tests (FVC)
- SNIP
- Haematology tests (FBC, ESR)
- Coagulation tests (to include INR, APTT and PT)
- Biochemistry tests (Troponin I, C-reactive protein (CRP), Glucose, Calcium)
- Creatinine Kinase
- Urea & Electrolytes (U&Es), Liver Function Tests (LFTs)
- Thyroid Function Tests (TSH, Free T4)
- Immunoglobulins (IgG, IgM)
- Quality of Life questionnaire (ALSAQ-40)
- Urinary p75ECD
- NfL levels
- Collection of exploratory biomarker blood samples
- Pregnancy test for WOCBP
- Adverse Event assessment/reporting

**Follow-up schedule 2 weeks after final IMP Administration**

- ALSFRS-R
- Concomitant drug history
- Vital signs (blood pressure, heart rate, body temperature, pulse oximetry and respiration rate). Results of oximetry should be the average of three recordings. Body weight and Body Mass Index (BMI)
- ECG
- Lung Function Tests (FVC)
- SNIP
- Haematology tests (FBC, ESR)
- Coagulation tests (to include INR, APTT and PT)
- Biochemistry tests (Troponin I, C-reactive protein (CRP), Glucose, Calcium)
- Creatinine Kinase
- Urea & Electrolytes (U&Es), Liver Function Tests (LFTs)
- Thyroid Function Tests (TSH, Free T4)
- Immunoglobulins (IgG, IgM)
- Quality of Life questionnaire (ALSAQ-40)
- Urinary p75ECD
- NfL levels
- Collection of exploratory biomarker blood samples
- Pregnancy test for WOCBP
- Adverse Event assessment/reporting

For patients who continue treatment, an end of treatment visit will occur 2 weeks after the last ILB injection, following the sample assessment as detailed for week 24 above.

**Single Point Long-Term Remote Follow up Visit**

All patients will be invited to provide quality of life data during an 8 week single point remote follow-up visit period starting in Quarter 1 of 2021.

Patients will be asked to re-consent electronically. After electronic consent has been given, the visit will be completed by the ALS study clinician via video conference and the following assessed:

- ALSFRS-R
- ALSAQ-40
- Concomitant medication including any current ALS treatment

---

